### Adherence measurement and motivation strategies

2.8

Attendance is recorded by the physiotherapist after each session. Additionally, patients are required to log their exercise progression in personal diaries, ensuring comprehensive tracking of their engagement and progress. We will employ strategic communication methods to bolster participation and adherence, including SMS reminders and phone calls. These reminders serve not only to motivate but also to provide timely prompts for upcoming sessions, thereby aiming to enhance overall engagement and consistency in participation.

Adherence to the intervention will be assessed at the 6-month follow-up as the number of exercise sessions attended out of the total number of sessions available. Satisfactory adherence will be attained when completing 36 out of 48 sessions (75%).

### Outcome parameters and assessment timeline

2.9

Outcome measures and assessment timeline are depicted in **Table 2**. In brief:

**Table 2 T2:** Timeline of key assessments and measurements throughout the study period.

Assessment	Baseline	3 M (PE)	6 M (PE)	12 M	24 M
Physical excerise randomised clinical Trial					
**Gait Impairment:** 6-Minute Walk Test (6MWT), MS Walking Scale 12 (MSWS-12)	✓	✓	✓	✓	✓
**Measurement of Physical Activity:** International Physical Activity Questionnaire-Short Form (IPAQ-SF)	✓	✓	✓	✓	✓
**Cardiorespiratory Fitness:** Ekblom-Bak test (sub-maximal cycle ergometer test)	✓	✓	✓		
**Adverse Events (AE) and Serious Adverse Events (SAE):**	✓	✓	✓	✓	✓
**Adherence to Intervention:** the proportion of attended sessions to total sessions available	✓	✓	✓	✓	✓
Prospective longitudinal data collection					
**Demographics:** Age (year), Sex, Race/Ethnicity, Geographic location, Height (cm), Education level, Marital status, Work status	✓				
Weight (Body Mass Index (BMI), Waist Circumference)	✓	✓	✓	✓	✓
**Medical history:** Diagnosis, Disease onset, Attack/Relapse History (Number of Relapse(s)**), Current Symptoms and Complaints, Vaccination History, Previous Infections; Fertility History, Previous injuries/surgeries, Family medical history, Dietary and Lifestyle Factors, Treatment’s status; Relapse Therapy; Full Drug List	✓	✓	✓	✓	✓
**Comorbid conditions:** Date of diagnosis, the severity (when available), the number of comorbid conditions grouped by main categories, and the actual raw numbers.	✓	✓	✓	✓	✓
**Risk factors:** Smoking, Alcohol consumption,	✓	✓	✓	✓	✓
**Neurological Examinations:** EDSS***, Hand grip force (hand−held dynamometer, 3x each side), Timed tests (T25−FW, 9−HPT), Visuo−perceptive motion analysis PASS−MS (short walks, static balance, stand−up and sit, stepping in place, finger tapping, finger−nose test) Spasticity assessment (Modified Ashworth Scale)	✓		✓	✓	✓
**Patient Reported Outcomes (PRO):** EuroQol 5-Dimension 5-Level Scale (EQ-5D-5L); Fatigue Severity Scale (FSS); International Physical Activity Questionnaire–Short Form (IPAQ-SF); Insomnia Severity Index (ISI); Modified Fatigue Impact Scale (MFIS); Patient Health Questionnaire-8 (PHQ-8); Pittsburgh Sleep Quality Index (PSQI); Visual Analog Scale (VAS).	✓	✓	✓	✓	✓
**Cognitive assessment:** Interview, Montreal Cognitive Assessment (MoCA), Symbol Digit Modalities Test (SDMT)	✓		✓		✓
**Biospecimens*** Blood samples, Cerebrospinal Fluid	✓		✓	✓	✓
**CNS magnetic-resonance imaging^*^** Cerebral: MPRAGE, T2−SPACE, FLAIR, MPM, DWI, rsfMRI Spinal: STIR (whole spine), PSIR (C2&C3 and C7/T1)	✓				✓

*Further details can be found in the method section.

** Number of Relapse(s) (a new or worsening acute neurologic symptom lasting ≥24 hours and not explained by fever or infection).

*** Disability assessment with alteration in EDSS score of at least 0.5 from baseline at the clinical visits.

"no evidence of disease activity" (NEDA-3) score will be calculated using data collected on relapses, EDSS, and MRI findings from the study.

The 6-Minute Walk Test (6MWT): The 6-Minute Walk Test (6MWT), as the primary outcome, quantitatively measures walking capacity, reflecting an individual’s endurance and mobility by recording the distance covered within six minutes on a hard, flat surface (82, 83).Physical exercise and cardiorespiratory fitness: The assessment framework encompasses a multifaceted approach to evaluating PE and cardiorespiratory fitness. The Ekblom-Bak test, a sub-maximal cycle ergometer assessment, will be employed to estimate maximal oxygen consumption (VO2 max). This test indirectly measures an individual’s cardiorespiratory fitness by analyzing the heart rate response to incremental exercise, which is a critical determinant of aerobic fitness and overall cardiovascular health (84, 85).Physical activity monitoring: Objective measurement of physical activity (PA) by accelerometers will be performed at baseline and at finalization of the study. Two Axivity AX3 accelerometers will be used to measure PA in each participant, who will wear the accelerometers attached to the skin, one attached to the front of the thigh using medical tape and the other to the non-dominant wrist using wristbands. In brief, skin-taped Axivity AX3 accelerometers have shown high compliance based on 24-h wear-time and has high data quality (86).Spasticity assessment: Spasticity will be evaluated using the Modified Ashworth Scale at baseline and at 6, 12, and 24 months. This standardized measure will allow for quantification of lower-extremity muscle tone and stiffness, complementing gait and disability assessments.Disability assessment: Disability assessment using EDSS with alteration in score of at least 0.5 from baseline regarded as significant.Relapse rate: Number of Relapse(s) (a new or worsening acute neurologic symptom lasting ≥24 hours and not explained by fever or infection).MRI of CNS: assessment of new or enlarged T2W or enhancing lesion indicating radiological diseases activity.Cognitive function: Cognitive functions will be evaluated using the Montreal Cognitive Assessment (MoCA). Participants’ education level and hand preference will be assessed through interviews (87).Patient-reported outcomes (PROMs): PROMs will be measured as a) PA level will be evaluated using the International Physical Activity Questionnaire-Short Form (IPAQ-SF) to categorize 3 groups of low, moderate, or high level of PA (88), b) current level of fatigue by the Modified Fatigue Impact Scale (MFIS) (89) and the Fatigue Severity Scale (FSS), c) quality of life using the European Quality of Life–5 Dimensions (EQ-5D-5L) (90) and d) depression level will be measured using the Personal Health Questionnaire Depression Scale (PHQ-8) (91) e) sleep quality and disturbances will be measured using the Pittsburgh Sleep Quality Index (PSQI) and the Insomnia Severity Index (ISI), which assess overall sleep quality and the severity of insomnia (92), respectively. f) Symptom intensity will be captured using a Visual Analog Scale (VAS), allowing participants to rate their perceived severity of pain.

### Biospecimens

2.10

Blood and CSF samples will be systematically collected at four key time points: baseline (prior to starting the exercise program), at 6 months (upon completion of the program), at 12 and 24 months. All clinical and laboratory data derived from these samples will be analyzed while maintaining blinding to ensure unbiased assessment. The markers of inflammation, metabolism and neurodegeneration include matrix metallopeptidase (MMP), vascular endothelial growth factor A (VEGF-A) and microfibril-associated protein 4, measured by ELISA. Selected cytokines interleukin (IL)-1beta, IL-6, IL-7, IL-10, IL-17A, tumor necrosis factor alpha (TNF-alpha), and NfL, Chitinase-3-Like-1, and Type I interferons, will be measured on a Quanterix™ Simoa HD-1 Analyzer using appropriate Simoa assay kits (93).

### MRI

2.11

Participants will undergo initial and final CNS MRI using a 3T system. This includes brain, spinal cord, and optic nerve imaging with sequences like 3D FLAIR, T2 SPACE, and T1 MPRAGE. Advanced techniques like multi-parametric mapping and diffusion-weighted imaging will be employed for detailed CNS characterization, focusing on changes related to MS and vascular comorbidities (94, 95).

### Adverse events

2.12

Adverse events (AE) will be systematically documented for both the intervention and the usual care group with a daily, pre-printed patient diary over the course of the 6-month period. Patients will report any symptoms or pain experienced post-PE. Both AE and serious adverse events (SAE) will be registered at all follow-up visits, employing open-ended questions to ensure comprehensive recording of all AEs. Additionally, patient medical records will be reviewed at 3 months during the program and at the primary endpoint (6 months) to identify any AEs that have occurred since enrollment. AEs will be classified in accordance with the Food and Drug Administration’s definition of SAE. The recording, categorization, and assessment of the severity of AEs will be conducted irrespective of presumed causality with study treatments. These evaluations will be conducted at 6 months post-intervention.

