#### Patients’ experiences with the feasibility study

2.20.2

By an individual conversation after exercise at the feasibility study the participants expressed their thoughts. They emphasized that the daily patient diary documentation for monitoring AE needed professional supervision. Participants experienced challenges incorporating digital exercise into their work-life routines. Observations further suggested that groups with having comparable age and PA levels tended to perform more cohesively. The positive experiences included the ease of logging in, the value of communication and the supervision performed by the physiotherapist. Moreover, a short structured post-exercise discussion with physiotherapist appeared to enhance social interaction and motivation.

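### The adverse-event diary goes to both arms, but the only report described for it is symptoms after exercise, so non-serious diary events are at risk of unequal ascertainment

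*Protocol article*

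**What the plan says.** Section 2.12 (Adverse events) opens with a rule for both arms: "Adverse events (AE) will be systematically documented for both the intervention and the usual care group with a daily, pre-printed patient diary", kept over the 6-month period. The next sentence gives the only description of what patients are to report: "Patients will report any symptoms or pain experienced post-PE". No equivalent is given for usual care or for days without exercise.

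The section adds two routes that are not tied to exercise. The first is questioning at visits: "Both AE and serious adverse events (SAE) will be registered at all follow-up visits, employing open-ended questions to ensure comprehensive recording of all AEs". The second is review of medical records at 3 and 6 months. It also says that AEs are recorded and graded "irrespective of presumed causality with study treatments".

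The section closes on timing: "These evaluations will be conducted at 6 months post-intervention". Table 1, item 11, lists the daily diary, with no mention of exercise, and places record review at the 6-month follow-up. Table 2 marks AEs at baseline and at 3, 6, 12 and 24 months.

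Section 2.20.2 reports feedback from the feasibility study that "the daily patient diary documentation for monitoring AE needed professional supervision".

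**The concern.** A safety summary by arm is fair only if both arms are asked the same question equally often. Here the diary is common to both arms, but its one described report hangs on an activity that the randomised programme delivers to one arm. If that wording is carried onto the printed page, an intervention participant with leg pain after a session has a line to fill in. A usual-care participant with the same pain on an ordinary day may have none. Equal true symptom rates could then give unequal diary counts, most plausibly higher in the intervention arm.

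Participants are not blinded (section 2.6), so self-reported symptoms are already open to differential reporting, and an exercise-anchored prompt adds to that. The events at stake are non-serious ones such as pain, which recall at visits months apart and medical records may miss. Diary data not collected during the 6 months cannot be recovered later.

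**Working it through.** The document states no AE rate, AE test or AE sample size, so there is no figure to reproduce. The check compares the texts and then counts reporting occasions.

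**What PE means.** The Introduction expands PE as physical exercise in general. In the trial procedures it names the randomised programme: the intervention is usual care plus the PE program (section 2.6), the primary endpoint runs to the end of the PE program (section 2.15), and Table 2 labels the 3- and 6-month columns with PE. Usual care is described as routine MS physiotherapy once weekly (section 2.7) and is not called PE. The procedural usage therefore points to one arm, but the article never says whether usual-care physiotherapy counts.

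**Anchor against causality rule.** Recording irrespective of causality means that timing relative to the study treatment should not decide whether an event is captured. A report limited to symptoms after exercise makes timing the filter. The two statements do not fit together unless the diary also holds a general item.

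**Reporting occasions per participant.** Inputs: 48 sessions over 24 weeks (Abstract and section 2.7); usual-care physiotherapy once weekly in both arms (sections 2.6 and 2.7). Assumption: every session is attended.

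- Diary days: 24 × 7 = 168
- Physiotherapy sessions: 24 × 1 = 24

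| Reading of the diary | Intervention | Usual care |
|---|---|---|
| Post-PE only, PE = trial programme | 48 | 0 |
| Post-PE only, weekly physiotherapy also counts | 48 + 24 = 72 | 24 (ratio 3:1) |
| General daily item in both arms, post-PE as an extra | 168 | 168 for the general item |

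**With feasibility attendance.** The 16 completers attended 243 of 16 × 24 = 384 sessions, or 63.3% (section 2.20). Applied to 48 sessions this gives 0.633 × 48 ≈ 30. The first row becomes about 30 against 0. The second becomes about 54 against 24, or 2.3:1, if physiotherapy is fully attended. The imbalance shrinks but stays.

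These are counts of occasions to report, not AE rates.

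**Timing.** The programme lasts 6 months. Six months after it, read literally, is 6 + 6 = month 12. The same section reviews records at months 3 and 6, and Table 1, item 11, gives only the 6-month follow-up. The three statements do not agree.

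**The case against.** The strongest reply is that the document never says post-exercise symptoms are the diary's only content. The diary is daily while sessions are twice weekly, so a page holding only post-session reports would make little sense. Table 1 mentions no such limit, and the form is not shown. On that reading the general part of the diary is balanced. This stands as a reason not to call bias established. It does not remove the point, because the general item has to be inferred, whereas the exercise-anchored report is stated.

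Three stronger readings are tempting, and the document does not support them.

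- A reader might infer that usual care has no exercise at all, so that the prompt can never apply there. Usual care includes weekly physiotherapy, and PE is first defined as exercise in general. The term is undefined for that arm, and occasions are far fewer or nil.
- A reader might infer that the whole between-arm AE comparison is biased. Open questions at visits and record review cover both arms and are not tied to exercise. No formal between-arm AE test is stated, and AEs are not among the named endpoints in section 2.15.
- A reader might infer from the feasibility feedback that only the intervention arm would get help with the diary. Section 2.20.2 does not say who would supervise it, and both arms have physiotherapy contact and follow-up visits.

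Nor does the feasibility study show heavy over-reporting. It followed the same procedures and reported no intervention-related AEs. That statement covers related events only and gives no AE result for usual care, so it settles nothing either way.

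**Conclusion.** The point holds in a limited form. As written, the diary's one described report is anchored to exercise, is undefined for usual care, and conflicts with the rule to record AEs regardless of causality. Non-serious AEs captured only by the diary are therefore at risk of unequal ascertainment between unblinded arms. Serious AEs, and anything found at visits or in records, are much less exposed.

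In reporting occasions, the gap runs from none (a general daily item exists), through 3:1, to wholly one-sided (48 against 0), at full attendance. The text does not settle which applies.

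The size of any bias in AE counts cannot be computed. One could assume that 2–10% of sessions yield a report and obtain 48 × 150 × 0.02 to 0.10 = 144 to 720 extra events in 150 intervention participants. That yield has no basis in the document, the product assumes full attendance, and the zero for usual care presupposes the reading in dispute. It should not be cited as an estimate.

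The timing mismatch is minor and separate. It needs reconciling but adds no weight to the diary point.

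**What to change.** In section 2.12 and on the diary page:

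- Use one daily item that does not mention exercise, worded identically in both arms, for example any new or worsened symptom, pain, fall or injury that day.
- Add a separate item, for the intervention arm only, for symptoms during or after a session.
- State that any between-arm AE summary rests on the neutral item together with the visit and record-review data, and that the session item is descriptive for the intervention arm.
- Reconcile the closing sentence on when AEs are evaluated with the record review at 3 and 6 months in the same section and with Table 1, item 11.

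The cost is a slightly longer diary page and a few sentences of protocol text. If the diary cannot be changed, the fallback is to state that diary AEs will not be compared between arms.

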### Data management

2.13

The data related to this study will be stored in the REDCap database system (96). This electronic platform is chosen for data collection and storage to ensure optimal data uptake.

### Data monitoring and auditing

2.14

Monthly data monitoring will be conducted using a REDCap query function for completeness and accuracy by the research team to ensure that any errors or inconsistencies are identified and addressed in a timely manner.

### Outcome measures

2.15

The primary endpoint will be evaluation of walking capacity by 6MWT from baseline to end of the PE program: (at baseline, 3, 6, 12 and 24 months).

Secondary outcomes include a “no evidence of disease activity” (NEDA-3) score characterized by three parameters 1) lack of clinical relapses, 2) disease progression measured by EDSS, and 3) MRI lesion data, e.g. absence of new T2 lesion/enhancing lesion, after two years’ observation (97–100). In addition, secondary endpoints include measures of quality of life and fatigue, as well as levels of cardiorespiratory fitness and neurofilament light chain (NfL) levels.

The role of comorbidity within the study design, including use as a stratification variable during randomization and as a prespecified covariate and potential effect modifier in the statistical analyses. In addition, the Charlson Comorbidity Index (CCI) will be used to quantify comorbidity burden in pwMS (101).

The efficacy of the interventions on comorbidities will be determined by using a combination of both objective physical tests, patient-reported outcomes and clinical/biochemical markers from baseline to post-intervention to assess outcome.

### Ethical considerations

2.16

The study was approved by The Regional Committee on Biomedical Research Ethics (Ref. no. S-20230011) and registered by ClinicalTrials.gov registration: NCT06298201. In addition, the study will be registered at the Danish Data protection agency. It will be conducted in accordance with the guidelines for good clinical practice set forth by the International Conference on Harmonization.

### Sample size calculation

2.17

A sample size calculation for the PE RCT was conducted to assess the effect of the intervention on the primary outcome, the 6-Minute Walk Test (6MWT), while accounting for comorbidity status and any potential interaction between comorbidity and the intervention. The calculation was based on:

A two-way factorial design incorporating intervention group (PE vs. control) and comorbidity status (yes/no) as binary factors, with a binary outcome based on the 6MWT, reflecting whether participants achieved a clinically meaningful improvement.A logistic regression model including intervention, comorbidity, and their interaction term as covariates.

The null hypothesis (H_0_) of no treatment effect was tested against the alternative hypothesis (H_1_) as either a main effect of the intervention or a significant intervention–comorbidity interaction, using a chi-square test derived from the logistic regression model.

Assumptions for the calculation were as follows: in the control group, it was assumed that 40% of participants with comorbidity and 20% without comorbidity would fail to achieve a clinically meaningful improvement in 6MWT. In contrast, in the intervention group, these proportions were expected to be reduced to 10% and 20%, respectively. This corresponds to a relative risk of 0.5, which is considered clinically significant.

Based on 10,000 simulation runs, a total of 73 participants per combination of intervention and comorbidity status (i.e., 292 participants in total) would be required to achieve approximately 80% statistical power at a 5% significance level. The simulations were performed using R software, version 4.1.2.

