Despite the benefits of PE for MS patients, a significant proportion drop out or fail to maintain an active lifestyle post-rehabilitation (53, 54). This trend is a serious challenge for integrating and sustaining PE in the daily lives of pwMS. Consequently, solutions that can support pwMS in sustaining a physically active lifestyle are warranted. A promising category of potential solutions covers eHealth devices and digital healthcare tools (55–59). The effectiveness of e-based MS rehabilitation, including telerehabilitation, has shown promising results in improving fitness, gait, balance, and upper limb function, often equaling or exceeding traditional treatment (60–64). Excluding pwMS from clinical trials based on the presence of comorbidity is common, which consequently leads to limited reports about the effect of comorbidities on outcomes of rehabilitation trials (65). Further research is required to investigate e-based PE’s effectiveness and long-term impact on managing pwMS with comorbidities. Significant knowledge gaps exist on the effect of PE on pwMS and comorbidities. The adaptation of exercise to comorbidity evidently adds challenges and complexity as to the application and integration of behavior change techniques, which may be applied to the exercise plan. Furthermore, most existing studies have excluded pwMS that had comorbidities at baseline (66). Accordingly, guidance and guidelines are not yet available for pwMS with comorbidity.

The aim of this randomized clinical trial (RCT) is to investigate if e-based PE, in addition to usual care, will be more effective than usual care alone in improving health outcomes for pwMS with and without comorbidities. Because the intervention focuses on progressive resistance training of the lower extremities, the 6-Minute Walk Test (6MWT) was chosen as the primary endpoint, reflecting expected improvements in walking endurance and functional mobility. Secondary endpoints capture disease activity and broader health impact, including NEDA-3 (relapses, EDSS progression, MRI activity), as well as measures of cardiorespiratory fitness (Ekblom–Bak test), accelerometer-measured activity, quality of life, fatigue, mood, sleep, pain, and biomarkers such as levels of neurofilament light chain (NfL).We hypothesize that PE significantly reduces disability, increasing walking capacity as the primary outcome for pwMS and comorbidity.

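### The 80% power in section 2.17 belongs to a joint test of treatment effect or interaction, which is not the trial's stated aim

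*Protocol article*

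**What the plan says.** The Introduction sets the aim: e-based exercise, added to usual care, "will be more effective than usual care alone in improving health outcomes for pwMS with and without comorbidities". The hypothesis sentence that closes the same section speaks of "increasing walking capacity as the primary outcome for pwMS and comorbidity", which can be read as covering only patients with comorbidity.

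Section 2.17 (Sample size calculation) makes 6MWT a binary outcome, whether or not a clinically meaningful improvement is reached. It uses this model: "A logistic regression model including intervention, comorbidity, and their interaction term as covariates". The null hypothesis of no treatment effect is set against "either a main effect of the intervention or a significant intervention–comorbidity interaction", "using a chi-square test derived from the logistic regression model". The degrees of freedom and the type of chi-square test are not given.

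The rates are: "in the control group, it was assumed that 40% of participants with comorbidity and 20% without comorbidity would fail"; with the intervention, "these proportions were expected to be reduced to 10% and 20%, respectively". The text adds: "This corresponds to a relative risk of 0.5, which is considered clinically significant". The result is 73 participants per combination of arm and comorbidity status, 292 in total, for about 80% power at the 5% level.

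Section 2.18 (Statistical analysis) plans an intention-to-treat analysis of longitudinal change by a multivariable regression model. It names no treatment contrast as confirmatory. Section 2.15 lists comorbidity as a covariate and potential effect modifier.

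**The concern.** The aim is directional and concerns one contrast, intervention against control. The alternative in section 2.17 is a composite. It is met if the intervention works on average, or if its effect merely differs between patients with and without comorbidity. A chi-square test of that composite does not look at the direction of effect, so it can be significant with no average benefit.

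Two things are at stake. First, the only formal hypothesis in the article is not the one the trial sets out to answer, and nothing in section 2.18 replaces it. Second, the 80% is the power of neither the treatment comparison nor the interaction. A reader who sees the interaction in the sample-size model may credit the trial with an ability to detect effect modification that the figure does not establish.

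**Working it through.** **Inputs (section 2.17).** n = 73 per cell, alpha 5%. Control failure rates are 40% with comorbidity and 20% without. The intervention rates have two readings:

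- A relative risk of 0.5 in each stratum: 40→20 and 20→10.
- The rates in printed order: 40→10 and 20→20. These are relative risks of 0.25 and 1.0, so 0.5 holds in neither stratum.

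**Step 1: reproduce the 80%.** The 2×2 logistic model was simulated with 73 per cell.

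| Test | 40→20, 20→10 | 40→10, 20→20 |
|---|---|---|
| Joint treatment + interaction, 2 df, Wald | 80.8% | 98.0% |
| Joint treatment + interaction, 2 df, likelihood ratio | 82.3% | 98.3% |
| Treatment, 1 df, adjusted for comorbidity | 88.5-88.7% | about 88% |
| Interaction, 1 df | about 6% | 83-85% |

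Only the joint 2-df test under a relative risk of 0.5 gives about 80%; the Wald version reaches 80% at about 72 per cell, against 73 stated. Other constructions under the same rates do not fit: counting success on either of two 5% likelihood-ratio tests gives 89.3%, either coefficient of the interaction model by Wald gives 41.8%, and a 3-df overall test gives 97.4%. In printed order the joint test already reaches 80% near 36 per cell.

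**Step 2: see by hand where the power comes from (relative risk 0.5).** The log odds ratio in each stratum has variance equal to the sum of 1/[n p(1−p)] over its two cells.

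- With comorbidity: OR = (0.20/0.80)/(0.40/0.60) = 0.375; log OR = −0.981; variance = 1/(73×0.24) + 1/(73×0.16) = 0.1427.
- Without comorbidity: OR = (0.10/0.90)/(0.20/0.80) = 0.444; log OR = −0.811; variance = 1/(73×0.16) + 1/(73×0.09) = 0.2378.
- Joint noncentrality: 0.981²/0.1427 + 0.811²/0.2378 = 6.74 + 2.77 = 9.51. On 2 df this gives a large-sample power of about 79%.
- Interaction part: (0.981 − 0.811)²/(0.1427 + 0.2378) = 0.170²/0.3805 = 0.08.
- Treatment part: 9.51 − 0.08 = 9.43. On 1 df this gives about 87%; the simulated figure is 88.5-88.7%.

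Almost all the information is in the treatment contrast. The second degree of freedom adds 0.08 to the noncentrality and costs about 8 points of power.

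**Step 3: power of the interaction.** Relative risk 0.5: z = 0.170/√0.3805 = 0.275; power = Φ(0.275 − 1.96) + Φ(−0.275 − 1.96) = 0.046 + 0.013 = 5.9%, close to alpha. Printed order: the odds ratios are (0.10/0.90)/(0.40/0.60) = 0.167 and 1.0, so the log odds ratios differ by 1.792. The same four rates give the same standard error, 0.617; z = 2.90 and power is about 83% (83-85% with simulation).

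**Step 4: can the joint test reject with no average benefit?** These examples are assumed, not taken from the article, with 73 per cell:

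- 40→20 with comorbidity and 20→40 without: joint test about 93%, 1-df test about 4%.
- 30→15 and 15→30: joint test about 79-81%, 1-df test about 5%.

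**Step 5: how often does this matter under the design assumptions?** With a relative risk of 0.5 in both strata, the joint test is significant without a significant 1-df treatment effect in about 1% of trials.

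**The case against.** The composite hypothesis appears in the sample-size section and describes what the simulation tested. Section 2.18 does not adopt it as the rule for success, and an analysis plan may exist that is not shown. This stands. A reader might infer that a positive trial could not show that exercise beats usual care, but the article does not support that, because it commits to no such decision rule. Under the rates that give 80%, the joint and the 1-df tests agree in nearly every trial. The opposite-effects examples are constructed, and nothing in the article suggests that such effects are expected.

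A reader might also take the either/or wording as two separate 5% tests, with an error rate near 9.7%. The article does not support this. It speaks of one chi-square test, and its 80% matches the joint test, which holds its size at about 5%; two tests would give about 89% power.

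Nor does the article claim separate power for the interaction; it says only that a potential interaction was accounted for. The 6% rests on the relative risk of 0.5, and the printed rates reverse it. The comorbidity-only hypothesis is one loosely worded sentence beside a clear aim.

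What survives is that the stated power is tied to a hypothesis that differs from the aim, and that no named contrast in section 2.18 takes its place.

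**Conclusion.** The point holds for the hypothesis and the power statement. The stated 80% is the power of a joint, non-directional 2-df test under a relative risk of 0.5 in both strata. It does not describe the comparison in the aim, for which the same 292 patients give about 88-89% before dropout on the binary outcome. The sample is therefore not too small for that comparison: about 57-58 per cell (228-232 in total) would give 80%.

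The low interaction power, about 6%, is conditional. It applies under the relative risk of 0.5, the only reading that reproduces the stated size. Under the printed order it would be about 85%, with joint power of 98%. The article contradicts itself here, and no statement about the interaction is safe until the rates and the relative risk are reconciled.

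All these figures are for the binary outcome of section 2.17. They do not carry over to the longitudinal change analysed in section 2.18.

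**What to change.** 1. Reconcile the failure rates in section 2.17 with the relative risk of 0.5.
2. State one primary hypothesis: the intervention effect on 6MWT at 6 months in all randomised patients, by one 1-df two-sided 5% test adjusted for comorbidity status.
3. Use the same form of 6MWT, binary responder or change, in sections 2.17 and 2.18.
4. Restate the power for that test. If the binary outcome and the relative risk of 0.5 are kept, it is about 88-89% before dropout. If change is chosen, a new calculation is needed.
5. Report the intervention-by-comorbidity interaction and both stratum effects as secondary estimates with 95% confidence intervals, outside the success rule, and state the interaction's own power.
6. Align the hypothesis sentence in the Introduction with the aim.

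The cost is wording in sections 1, 2.17 and 2.18, plus a recalculation if change is chosen; with the binary outcome under the relative risk of 0.5, no patients are added. The price is that, under that relative risk, the interaction is openly labelled as having little power.
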